---

## 1. STUDY GLOSSARY

| Abbreviation or Term | Definition/Explanation                                         |
|----------------------|----------------------------------------------------------------|
| GCP                  | Good Clinical Practice                                         |
| GMP                  | Good Manufacturing Practice                                    |
| CRF                  | Case Report Form                                               |
| SAE                  | Serious Adverse Event                                          |
| SOP                  | Standard Operating Procedure                                   |
| BMD                  | Bone Mineral Density                                           |
| ECG                  | Electrocardiogram                                              |
| SD                   | Standard Deviation                                             |
| ALT                  | Alanine Aminotransferase                                       |
| AST                  | Aspartate Aminotransferase                                     |
| TCM                  | Traditional Chinese Medicine                                   |
| Cr                   | Creatinine                                                     |
| ICF                  | Informed Consent Form                                          |
| IRB                  | Institutional Review Board                                     |
| PI                   | Principal Inspector                                            |
| CFDA                 | Chinese State Food and Drug Administration                     |
| DXA                  | Dual X-ray Absorptiometry                                      |
| BSYJF                | Bushen Yijing Fang                                             |
| DDIPA                | Questionnaire for daily dietary intake and physical activities |
| TUG                  | Timed Up and Go Test                                           |
| ITT                  | Intent to Treat                                                |
| HPLC                 | High-performance Liquid Chromatography                         |
| ANOVA                | Analysis of Variance                                           |
| LOCF                 | Last Observation Carry Forward                                 |

## 2. PROTOCOL SYNOPSIS

|                      |                                                                                                                                                                                                                                                                                                                                                                                                                                                                                                                                                                                                                                                                                                                                                                                                                                                                                                                                                                                                                                                                                                      |
|----------------------|------------------------------------------------------------------------------------------------------------------------------------------------------------------------------------------------------------------------------------------------------------------------------------------------------------------------------------------------------------------------------------------------------------------------------------------------------------------------------------------------------------------------------------------------------------------------------------------------------------------------------------------------------------------------------------------------------------------------------------------------------------------------------------------------------------------------------------------------------------------------------------------------------------------------------------------------------------------------------------------------------------------------------------------------------------------------------------------------------|
| Protocol name        | The effects and safety of Bushen Yijing Fang (BSYJF) reduces hip fractures risk factors in late postmenopausal women with osteopenia: A long-term follow-up, randomized, double-blind and placebo-controlled trial                                                                                                                                                                                                                                                                                                                                                                                                                                                                                                                                                                                                                                                                                                                                                                                                                                                                                   |
| Sponsor              | Shanghai Shuguang Hospital                                                                                                                                                                                                                                                                                                                                                                                                                                                                                                                                                                                                                                                                                                                                                                                                                                                                                                                                                                                                                                                                           |
| Indication           | Late postmenopausal women with osteopenia                                                                                                                                                                                                                                                                                                                                                                                                                                                                                                                                                                                                                                                                                                                                                                                                                                                                                                                                                                                                                                                            |
| Purpose              | To evaluate long-term efficacy of BSYJF on hip fracture risk factors in late postmenopausal women with osteopenia.                                                                                                                                                                                                                                                                                                                                                                                                                                                                                                                                                                                                                                                                                                                                                                                                                                                                                                                                                                                   |
| Design               | Randomized, 36-month, double-blind and placebo-controlled trial                                                                                                                                                                                                                                                                                                                                                                                                                                                                                                                                                                                                                                                                                                                                                                                                                                                                                                                                                                                                                                      |
| Simple size          | 140 subjects (70 per group)                                                                                                                                                                                                                                                                                                                                                                                                                                                                                                                                                                                                                                                                                                                                                                                                                                                                                                                                                                                                                                                                          |
| Setting              | Two sites                                                                                                                                                                                                                                                                                                                                                                                                                                                                                                                                                                                                                                                                                                                                                                                                                                                                                                                                                                                                                                                                                            |
| Intervention time    | From 2000-01-01 To 2004-12-31                                                                                                                                                                                                                                                                                                                                                                                                                                                                                                                                                                                                                                                                                                                                                                                                                                                                                                                                                                                                                                                                        |
| Eligibility criteria | 
Inclusion:
 
 
1. Women with at least 10 years natural menopause, and aged from 55 to 69 years;
 
2. Osteopenia at least 12 months (T-score between -2.5 and -2 SD at femoral neck).
 
 
Exclusion:
 
 
1. Who had been diagnosed as having a neurological or musculoskeletal disorder, or coexisting chronic diseases;
 
2. Who have taken estrogen and calcitonin, fluoride, bisphosphonates, or adrenocortical hormone within one year;
 
3. Who had been took <math>\geq 4</math> prescription medications;
 
4. has environmental hazards for falls or tripping;
 
5. has impairment in gait;
 
6. has postural hypotension: drop in systolic blood pressure <math>\geq 20\text{mmHg}</math> or to <math>< 90\text{mmHg}</math> on standing;
 
7. has impairment in transfer skills or balance;
 
8. has impairment in leg or arm muscle strength or range of motion (hip, ankle, knee, shoulder, hand, elbow) ;
 
 |

|                            |                                                                                                                                                                                                                                                                                                                                                                                                                                                                                                                                                                                                                                                                                                                                                                                                                                                                 |
|----------------------------|-----------------------------------------------------------------------------------------------------------------------------------------------------------------------------------------------------------------------------------------------------------------------------------------------------------------------------------------------------------------------------------------------------------------------------------------------------------------------------------------------------------------------------------------------------------------------------------------------------------------------------------------------------------------------------------------------------------------------------------------------------------------------------------------------------------------------------------------------------------------|
|                            | 9. has ALT or AST levels greater than 50% of upper normal limit; serum creatinine levels greater than 133 $\mu$ mmol/l or 1.5 mg/dl.                                                                                                                                                                                                                                                                                                                                                                                                                                                                                                                                                                                                                                                                                                                            |
| Drug administration        | 300mg element calcium daily with either BSYJF capsules (3 capsules per time, 3 times per day) or placebo.                                                                                                                                                                                                                                                                                                                                                                                                                                                                                                                                                                                                                                                                                                                                                       |
| Study period               | 36-month                                                                                                                                                                                                                                                                                                                                                                                                                                                                                                                                                                                                                                                                                                                                                                                                                                                        |
| Endpoints                  | 
Endpoints are to be evaluated for BSYJF versus placebo.
 
Primary endpoints:
 
 
1. Change from month baseline at month 36 in femoral neck BMD;
 
2. Change from month baseline at month 36 in lean mass of left thigh;
 
3. Change from month baseline at month 36 in TUG test;
 
4. The number of falls at month 36.
 
 
Secondary endpoints:
 
 
1. Change from month baseline at month 36 in biomarkers of bone turnover (osteocalcin and deoxypyridinoline).
 
2. Change from month baseline at month 36 in endometrial thickness;
 
3. Change from month baseline at month 36 in estradiol;
 
4. Nature, frequency and severity of adverse events and their relationship to treatment.
 
 |
| Statistical considerations | 
All the analyses will use randomly assigned patients under ITT principle. For patients missing data, the LOCF approach use to analyze the longitudinal data. Repeated-measures ANOVA analysis should be carried out between two groups and four times (baseline, 12, 24 and 36 months). Within-subjects results will be used t-test on the percentage change from the baseline value. The number of falls and adverse events will perform by chi-square test. All tests will be used two-sided and set at the 5% level.
                                                                                                                                                                                                                                                                                                                           |

### 3. BACKGROUND AND RATIONALE

#### 3.1 Hip fractures

Hip fractures cause disability and even mortality in community-dwelling elderly women, which is a devastating consequence of osteoporosis (Cooper and Barker, 1995; Zuckerman, 1996). Although many factors contribute to such fractures, the most important causes are a reduction in bone mass and an increased frequency of falls (Chapuy and Arlot et al., 1992). It is estimated that approximately 90% hip fractures in late postmenopausal women resulted from a fall (Zuckerman, 1996). It has been known that the deteriorated muscle and impaired functional mobility increases the falling risk factors obviously (Greenspan and Myers et al., 1994). Thus, it indicates that the bone-dependent risk factors including decreased bone mass and deteriorated bone micro-architecture are not the only determinant of hip fracture. In other words, the bone-independent risk factors including decreased muscle and functional mobility also play an important role in hip fracture risk factors in late postmenopausal women.

The conventional medications for preventing hip fractures only focus on bone-dependent risk factors by either inhibiting bone resorption (bisphosphonates) or promoting bone formation (rhPTH). Despite that supplement of vitamin D has demonstrated beneficial effects on muscle, there is still lack of high quality evidence to support that vitamin D alone could prevent hip fractures effectively, especially for the late postmenopausal women with osteopenia (Chapuy and Arlot et al., 1992). Therefore, it is desirable to develop alternative medications that can exert beneficial effects on reducing both bone-dependent and bone-independent risk factors.

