## 7. SUBJECT ENROLLMENT PROCEDURES

### 7.1 Study Visit Definitions

Screening date is defined as the date that the ICF is signed. Enrollment date is defined as the date of randomization. The randomization must be completed within 2 weeks of the screening date (or re-screened within 2 weeks). If a subject's visit is delayed, her subsequent visit should not be shifted.

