## 9. DRUG ADMINISTRATION

### 9.1 Packaging and Formulation

All the participants will be received daily calcium carbonate 300 mg as the basic treatment. The participants will be orally given BSYJF capsules or placebo capsules (3 capsules per time, 3 times per day) for 36 months. All the capsules should package in identical plastic bottles (100 capsules per bottle) and subsequently delivered to the participants every 3 month at each clinical visit. All the participants will be told to take the capsules with element calcium before meal. The quality control for screening and verification of adherence to the protocol will perform by the supervisor. BSYJF/placebo will be manufactured, packaged, and distributed by Shuguang Hospital.

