### 12.4 Laboratory Assessments

All screening and on-study samples will be processed and sent to the laboratory. The laboratory will be responsible for performing the assays. Biochemical examination (complete blood count, renal function, liver function and 25-OH-vitamin D), blood pressure and observation of abnormal symptoms/signs based on standardized patient report forms performs at

baseline and 12, 24, and 36 months (Table 1). Serum osteocalcin or urine deoxypyridinoline is as a marker predicting hip fracture in elderly women (Szulc and Chapuy et al., 1996). Serum 25-OH-vitamin D, osteocalcin, 17 $\beta$ -estradiol and urine deoxypyridinoline should be obtained in the morning after an overnight fast and be delivered to the laboratory for measurements using commercial kits.

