**Secondary endpoints:**

- (1) Change from month baseline at month 36 in femoral neck BMD;**
- (2) Change from month baseline at month 36 in lean mass of left thigh;**
- (3) Change from month baseline at month 36 in TUG test;**
- (4) Change from month baseline at month 36 in osteocalcin;
- (5) Change from month baseline at month 36 in deoxypyridinoline;
- (6) Changes from baseline at month 36 in estradiol;
- (7) Change from month baseline at month 36 in endometrial thickness;
- (8) Nature, frequency and severity of adverse events and their relationship to treatment.

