| Eligibility criteria | 
Inclusion:
 
 
1. Women with at least 10 years after natural menopause, and aged from 55 to 69 years;
 
2. Osteopenia at least 12 months (T-score between -2.5 and -2 SD at femoral neck).
 
 
Exclusion:
 
 
1. Who had been diagnosed as having a neurological or musculoskeletal disorder, or coexisting chronic diseases;
 
2. Who have taken estrogen and calcitonin, fluoride, bisphosphonates, or adrenocortical hormone within one year;
 
3. Who had been took <math>\geq 4</math> prescription medications;
 
4. has environmental hazards for falls or tripping;
 
5. has impairment in gait;
 
6. has postural hypotension: drop in systolic blood pressure <math>\geq 20</math>mmHg or to <math>< 90</math>mmHg on standing;
 
7. has impairment in transfer skills or balance;
 
8. has impairment in leg or arm muscle strength or range of motion (hip, ankle, knee, shoulder, hand, elbow) ;
 
9. has ALT or AST levels greater than 50% of upper normal limit; serum creatinine levels greater than 133<math>\mu</math>mol/l or
 
 |

|                                   |                                                                                                                                                                                                                                                                                                                                                                                                                                                                                                                                                                                                                                                                                                                                                                                                                                                                                                                                                                            |

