|--|----------------------------------------------------------------------------------------------------------------------------------------------------------------------------------------------------------------------------------------------------------------------------------------------------------------------------------------------------------------------------------------------------------------------------------------------------------------------------------------------------|
|  | 
analysis providing a 95% confidence interval. Repeated-measures ANOVA analysis should be carried out between two groups and four times (baseline, 12, 24 and 36 months). Within-subjects results will be used t-test on the mean percentage change from the baseline value. All tests will be used two-sided and set at the 5% level.
 
Additional analysis:
Number of falls at the end of 10 years extension follow-up will be performed by chi-square test.
 |
|--|----------------------------------------------------------------------------------------------------------------------------------------------------------------------------------------------------------------------------------------------------------------------------------------------------------------------------------------------------------------------------------------------------------------------------------------------------------------------------------------------------|

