**Additional endpoint:**

**Number of falls at the end of 10 years extension follow-up will be performed by chi-square test.**

Section: 17.2 Diet and Exercise Control

Add:

During the entire trial, the subjects will be advised to follow the guideline for daily dietary intake and physical activities, such as intaking high-protein diet, avoiding alcohol abuse and smoking, and keeping active in daily physical activities. The questionnaire for daily dietary intake and physical activities should be recorded at 12, 24, 36 months during 36-month clinical trial **and at the 3rd, 6th and 10th year during 10-year follow-up.** Calcium and vitamin D supplement on their own should be prohibited in 36-month clinical trial.

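### Women may enter while taking their own calcium or vitamin D and must then stop, so month-36 changes in secondary endpoints, chiefly lean mass and TUG, include stopping; adjust for baseline 25(OH)D

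*Supplement*

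**What the plan says.** Four parts of the plan bear on this point.

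- **Premise.** Section 3.1 states "Despite that supplement of vitamin D has demonstrated beneficial effects on muscle", while doubting that vitamin D alone prevents hip fracture.
- **Entry.** The only exclusion on earlier bone-active treatment (6.2(2), unchanged in the Amendment 2 synopsis) reads "Who have taken estrogen and calcitonin, fluoride, bisphosphonates, or adrenocortical hormone within one year". Calcium and vitamin D are not in it. Exclusion 3 counts prescription medicines only.
- **On study.** Section 17.2, as restated in Amendment 2, says "Calcium and vitamin D supplement on their own should be prohibited in 36-month clinical trial". Both arms receive trial calcium: "All the participants will be received daily calcium carbonate 300 mg as the basic treatment" (9.1; the synopsis calls it 300 mg of elemental calcium). No vitamin D is supplied.
- **Timing and analysis.** Under 7.1, "The randomization must be completed within 2 weeks of the screening date". Table 1 places lean mass, BMD and TUG at week 0. The secondary endpoints are changes from that baseline, for example "Change from month baseline at month 36 in lean mass of left thigh". The Amendment 2 synopsis prescribes a repeated-measures ANOVA between groups and, for within-subject results, a *t*-"test on the mean percentage change from the baseline value".

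Sections 7.4 and 12.4 have 25(OH)D measured at screening or baseline and at 12, 24 and 36 months. No analysis stated in 16.3 or the synopsis uses it.

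**The concern.** The plan treats women's own supplements as important enough to prohibit for three years, yet lets current users in and states no period off them before baseline. For such a woman, the change to month 36 is the effect of BSYJF or placebo plus whatever follows from stopping the supplement. On the plan's own premise the endpoints most exposed are lean mass and TUG, because 3.1 credits vitamin D with an effect on muscle and says nothing comparable about BMD or turnover markers.

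At stake are the precision of the secondary comparisons on the muscle and mobility pathway, and the meaning of any within-arm change. A fall in lean mass in one arm could reflect ageing, treatment or a stopped supplement, and the within-subject test cannot separate them.

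**Working it through.** **Does the text let the situation arise?** Exclusion 2 does not bar users, and exclusion 3 does not count supplements bought without prescription. No run-in is described. The documents do not say exactly when the ban starts. If it starts at randomisation, baseline is measured on supplements. If it starts at consent, at most about two weeks pass before baseline. Either way the change score of a prior user contains the stopping effect. For calcium the daily 300 mg replaces part of what is stopped; for vitamin D nothing does.

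**Size.** The plan gives no figure to reproduce here: neither the share of users nor the effect of stopping is stated. I assume a share *u* of 0.2 to 0.4 and a mean shift *w* of 0.3 to 0.6 SD of the change score, with *n* = 70 per arm (Amendment 2, 5.1).

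| Quantity | Formula | Low (*u*=0.2, *w*=0.3) | High (*u*=0.4, *w*=0.6) |
|---|---|---|---|
| Expected between-arm bias | *uw* − *uw* | 0 | 0 |
| Added variance | *u*(1−*u*)*w*² | 0.2×0.8×0.09 = 0.014 | 0.4×0.6×0.36 = 0.086 |
| SD multiplier | √(1 + added variance) | 1.007 | 1.042 |
| Equivalent *n* per arm | 70 / (1 + added variance) | 69.0 | 64.4 |
| Shift in each arm's mean change | *uw* | 0.06 SD | 0.24 SD |

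The loss of information equals about 1 to 6 women per arm. The standard error of a within-arm mean is 1/√70 = 0.12 SD before inflation, so the within-arm shift is 0.06/0.1195 = 0.5 standard errors at the low end. At the high end, allowing for the added variance, it is 0.24/(0.1195×1.042) = 1.9.

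A wider share with a smaller shift (10-50% users, 0.25-0.5 SD) gives a similar picture: the SD rises by 0.3-3.1% and each arm's mean change shifts by 0.025-0.25 SD.

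**Is the upper end generous?** Yes. The calculation for lean mass and TUG that Amendment 1 deleted gave 55 per group. A difference of 0.5 with SD 0.89, one-sided 5% and 90% power reproduces that: 2×(1.645+1.282)²×(0.89/0.5)² = 54.3, so 55. That difference is 0.5/0.89 = 0.56 SD. A stopping effect of 0.6 SD would exceed the drug effect once planned for.

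**The case against.** The strongest reply is that the trial's comparison is randomised, blinded and between arms. Stopping applies equally to both arms and cancels in expectation. This stands in full. A reader might infer that the BSYJF-placebo estimate is biased, but the documents do not support that. Nor should a chance imbalance in users be counted as a further error: it is the same added variance and is already in the observed standard error, so the type I error of the between-arm test is unaffected.

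Second, the primary endpoint since Amendment 1 is the number of falls, which is not a change score. This also stands; only secondary endpoints are touched.

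Third, a reader might say that the within-subject tests produce false positives. They do not, in the strict sense. If stopping lowers lean mass, the change is real and rejecting no change is correct. The fault would lie in the attribution, and the plan does not say how within-arm results will be interpreted. The *t*-test on percentage change may even be meant between arms, in which case only the variance remains.

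Fourth, covariates for secondary endpoints can be set in the separate analysis plan that 16.2 says will be finalised before database lock. That is fair. The adjustment is a low-cost improvement to the stated models, not proof of an omission.

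Finally, 3.1 also names rhPTH, which exclusion 2 does not list. Section 17.2 does not prohibit it either, so the same mismatch between entry and on-study rules does not arise.

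**Conclusion.** The concern holds in a limited form. The entry rule and the on-study ban do not match, and no washout links them, so prior users' month-36 changes in secondary endpoints include stopping their supplement. The point is strongest for vitamin D with lean mass and TUG. For BMD the documents give no comparable premise, and for calcium the trial supply offsets part of the change.

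The between-arm comparison remains unbiased. Its cost is about 1-9% more variance under assumed values of 20-40% users and a 0.3-0.6 SD shift, and the upper end is generous. Within an arm, the mean percentage change cannot be attributed to BSYJF or to natural loss. This is a minor point whose size depends wholly on figures the documents do not give. It merits a change because the main remedy is nearly free.

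**What to change.** 1. In 16.3, include baseline 25(OH)D as a covariate in the between-arm comparisons of lean mass and TUG, and of BMD if wished. Because the repeated-measures model treats baseline as one of its four time points, the covariate must enter with its interaction with time (or the model must be fitted to change from baseline). A main effect alone would not adjust the change.
2. Add prior supplement use as a covariate where the medication history records it. The documents do not show that self-bought supplements are captured, and Appendix F has no question on them, so an explicit item may be needed.
3. State that efficacy conclusions rest on the between-arm comparisons and that within-subject tests are descriptive.
4. Reconcile 6.2(2) with 17.2 and say when the ban begins. Whether prior users should be eligible is for the sponsor to decide.

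Items 1 and 3 need no further patients, visits or assays. Item 2 costs at most one question at screening. Baseline 25(OH)D is only a proxy for supplement use, so adjustment will recover part of the added variance, not all of it.
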